### Quality assurance and quality control

To ensure the quality of the study, otolaryngology experts in Chinese medicine, Western medicine, and statisticians will review and revise the study protocol prior to the start of the experiment. Other standardized procedures for research operations, including details such as filling out questionnaires, recruiting participants, treatment interventions, AE evaluation, and data management, have also developed uniform standards. Any deviations from the protocol will be fully documented using a breach report form. We will update the protocol in the clinical trial registry in the event of protocol modifications. The Project Management Group will meet every 3 months to review the trial conduct. The Clinical Medical Research Ethics Committee of the First Affiliated Hospital of Anhui Medical University will meet every half year to review conduct throughout the trial period. The clinical research assistant will periodically review the data to ensure the authenticity, timeliness, and data quality of the data collection. All data will be collected in the form of paper + electronic questionnaires, finally transferred to an Excel spreadsheet, and stored for at least 5 years after the trial results will be published. Therefore, all data collected during the research process will be kept strictly confidential and used only by researchers. The patient’s private information, including name and phone number, will be strictly protected and will never be allowed to be disclosed. If reviewers or readers have any questions about our published data, they can contact the corresponding author to obtain the data. Researchers will make detailed treatment plan descriptions, acupoint pictures, videos, and TEAS treatment procedures and distribute them to each participant. Researchers will ensure that the participants comply with the intervention plan. A specially established communication team will guide participants in their interventions and will be available to answer their questions. All treatments will be free of charge to participants, and for those who will discontinue or deviate from the intervention protocols, we will keep the data we have collected and record the reasons for quitting. Participants will be registered with a phone number and address for further contact if they miss the follow-up time.

### Statistical methods

#### Sample size

According to the previous literature on the use of PPI therapy in the Chinese population [38], after 3 months of LPRD treatment, the RSI score was approximately 11.7 points, and the standard deviation was approximately 6. We will estimate that the RSI score of the intervention group will be 4.5 points higher than that of the control group after treatment. Comparing two independent samples using a two-tailed *t*-test with an alpha value of 0.05% and 80% power, a sample size of 29 patients will be obtained. Considering a dropout rate of 10%, 33 patients will be recruited for each group. In actual recruitment, we will plan to recruit 35 participants for the intervention and control groups. We will plan to recruit sufficient participants by posting posters in ENT clinics for 4 months.

#### Statistical analyses

The measurement data that conform to the normal distribution will be represented by the mean ± standard deviation, and the measurement data that do not conform to the normal distribution will be represented by M (P25, P75). The analysis will be performed based on intention-to-treat and will be performed using SPSS version 23.0. A bilateral *P* value of less than 0.05 will be considered significant. Continuous variables will be compared using the t-test or Mann–Whitney *U* test. The chi-squared test or Fisher’s exact test will be used to compare the qualitative data.

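### The RSI analysis is labelled intention-to-treat, but the two-group tests named for it leave unused the baseline and earlier scores of any patient whose later visit is missing

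*Protocol article*

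**What the plan says.** In the protocol article, Statistical analyses fixes the population and the tests. The population: "The analysis will be performed based on intention-to-treat and will be performed using SPSS version 23.0". The tests: "Continuous variables will be compared using the t-test or Mann–Whitney *U* test", and for categorical outcomes "The chi-squared test or Fisher’s exact test will be used to compare the qualitative data". The significance rule is "A bilateral *P* value of less than 0.05 will be considered significant". No model for the repeated scores is named.

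The sections on the primary outcome and on Dx-pH monitoring schedule the RSI at baseline and at weeks 4, 12 and 24. The outcome is described as change in score.

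Sample size rests on RSI after three months of treatment and on a "two-tailed *t*-test with an alpha value of 0.05% and 80% power, a sample size of 29 patients will be obtained". It then adds an allowance for loss: "Considering a dropout rate of 10%, 33 patients will be recruited for each group". The planned number is 35 per group.

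Quality assurance and quality control says of patients who stop or deviate that "we will keep the data we have collected and record the reasons for quitting". It also provides for contacting patients who miss a follow-up visit. Adverse events has a participant leave the trial after a severe event. Randomization and allocation concealment makes the trial open to patients and outcome assessors. Only the TEAS arm has hour-long sessions, mostly at home, five times a week for 12 weeks.

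**The concern.** A two-group test at a visit needs one number per patient. If the week-12 score is missing, the test has nothing to work with, and that patient's baseline and week-4 scores play no part. This is so whether the test is run on the score or on the change from baseline: a change score brings in the baseline only for patients who also have the later score. The plan therefore collects and keeps information on patients who are later lost, and names a method that does not use it.

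This matters because the label promises a comparison of everyone randomised. If patients leave for reasons linked to how they felt at week 4, and do so differently in the two arms, those still present at week 12 no longer represent the arms as randomised. The trial has features that could produce this: open allocation, a self-reported primary outcome, and a treatment burden carried by one arm only. At stake are a shifted estimate of the RSI difference and a false-positive rate away from the nominal 5%.

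**Working it through.** **1. Reproduce the plan's sample size.** Inputs from Sample size: difference 4.5, SD 6, 80% power, two-sided test. Alpha is taken as 5%, because the printed percentage read literally would need 70 per group.
- Two-sample t-test (noncentral t): 29 per group, power 0.801. This matches the plan.
- Dropout: 29/0.9 = 32.2, rounded up to 33. This matches too.
- At the planned 35 per group, 10% loss leaves 35 × 0.9 = 31.5.

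So loss of about 4 patients per arm is within the plan's own expectation.

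**2. Bias of a comparison restricted to observed scores.** Let f be the share of the TEAS arm lost, and g the mean RSI of lost minus retained TEAS patients. The mean of the whole arm is (1 − f) × retained mean + f × lost mean = retained mean + f × g. The retained mean is therefore too low by f × g. If control loss is unrelated to outcome, this is the bias of the arm difference, and a positive value favours TEAS because a higher RSI is worse. The gap g is an assumption; no document gives it.

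| TEAS lost of 35 | g = +3 | g = +6 | g = −6 |
|---|---|---|---|
| 4 (11.4%) | 0.34 | 0.69 | −0.69 |
| 7 (20%) | 0.60 | 1.20 | −1.20 |
| 10 (28.6%) | 0.86 | 1.71 | −1.71 |

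If both arms lose the same share with the same gap, the two terms cancel and the bias is 0.

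**3. Effect on the false-positive rate**, with no true difference, 4 control patients lost at random, g = +6 and SD 6 kept for those retained:
- 4 TEAS lost: standard error 6 × √(1/31 + 1/31) = 1.52; shift 0.69/1.52 = 0.45 standard errors. The chance of a significant result in favour of TEAS is 6.5% instead of 2.5%; two-sided 7.3% instead of 5%.
- 7 TEAS lost: standard error 6 × √(1/28 + 1/31) = 1.56; shift 1.20/1.56 = 0.77. The corresponding chances are 11.4% and 11.7%.

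**4. Simulation with loss driven by the week-4 score.** Assumptions not in the documents: baseline RSI 20 (SD 5), baseline to follow-up correlation 0.4, week-4 to week-12 correlation 0.5 to 0.7, TEAS loss weighted to high week-4 RSI, control loss random, no true effect. The ranges span three separate simulations with somewhat different strengths of selection.

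| Patients lost | Bias of t-test towards TEAS | Two-sided false positives |
|---|---|---|
| 4 TEAS, 4 control | 0.4 to 0.7 points | about 5% to 9% |
| 7 TEAS, 4 control | 0.7 to 1.2 points | about 7.5% to 13% |

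With 4 lost per arm, adjusting the observed week-12 scores for baseline alone still leaves 0.3 to 0.6 points, because the selection runs through week 4. A likelihood estimate that uses baseline and week 4 has bias near 0 in every scenario. That includes a reversed one in which good responders leave TEAS: there the t-test is off by 0.53 points against TEAS and the likelihood estimate by 0.02. The likelihood estimate's standard error is also about 6% to 10% smaller.

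**The case against.** The strongest objection is that the article nowhere says patients with missing scores are deleted. A t-test can follow imputation, and the handling of missing data is commonly left to a full protocol or analysis plan, which is not shown. This stands: a completer analysis is an inference, and the lack of a missing-data rule is not the point made here. The point is the method that is named, which does not use repeated scores the trial collects.

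Raising 29 to 33 for dropout does not prove a completer analysis either. Such an allowance is routine under any method and shows only that some loss is expected.

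A reader might go further and infer that selective loss will bias the result towards TEAS. The documents do not support that. Nothing in them predicts greater loss from TEAS or says who would leave, and the Discussion expects good compliance. Control patients who know they lack TEAS and feel no better also have a reason to go. The sign reverses if responders leave, and the bias cancels if both arms lose patients by the same mechanism.

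Stopping home sessions is also not the same as a missing RSI: the questionnaire can still be completed, and re-contact is provided for. This lowers the likely loss but does not remove the 10% that the plan allows for.

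Finally, the simulation puts the asymmetry in by assumption. The mixed model does well there because missingness was made to depend on a score that it uses. That is fair, and it is why a sensitivity analysis belongs beside the model.

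**Conclusion.** The point holds in conditional form. The intention-to-treat label sits beside a method that, unless missing scores are dealt with first, takes nothing from a patient whose later visit is missing. Loss related to early response and differing between the arms can then bias the RSI comparison. A bias towards TEAS is plausible given its burden, but the direction is not settled.

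Under the illustrative assumptions the bias is about 0.4 to 0.7 points at the planned 10% loss, which is small against 4.5. It is about 0.7 to 1.2 points with 7 TEAS and 4 control patients lost, about twice the planned rate in the TEAS arm. These figures rest on an assumed gap or correlation and on random control loss. The change is worth making because it is cheap, helps whichever way the loss runs, and gains some precision. The calculations do not show that the trial's conclusion would be overturned at the planned loss.

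**What to change.** In Statistical analyses, replace the visit-wise two-group test for RSI by one linear mixed model for repeated measures over all post-baseline visits. Suitable text:

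*RSI at weeks 4, 12 and 24 will be analysed in all randomised patients with at least one post-baseline score, by a linear mixed model with arm, visit, arm-by-visit, baseline RSI and baseline-by-visit as fixed effects and an unstructured covariance (SPSS MIXED). The arm difference with 95% confidence interval will be reported at each visit, including week 12, the time point used for the sample size.*

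Add one sensitivity analysis in which missing TEAS scores take control-arm values. It should also include randomised patients with no post-baseline score, whom the model leaves out.

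The cost is a few lines of text and slightly more analysis work in the software already named, with no new patients, visits or data. The downside is small: the model assumes that missingness is explained by the observed scores, and the sensitivity analysis tests how far the result depends on that.

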**Methods:**

This prospective randomized controlled trial will be implemented in a tertiary hospital in China. Seventy patients diagnosed with LPRD will be randomly assigned to the TEAS + PPI group (intervention group) or PPI group (control group), at a ratio of 1:1. In addition to using PPI, the intervention group will receive TEAS at four groups of acupoints, and each group will be treated for 15 min, once for 60 min, five times a week, for 12 weeks, 60 times. The main outcome will be changes in the Reflux Symptom Index scores at 4, 12, and 24 weeks after treatment. The secondary outcomes will include changes in the reflux finding score, Laryngopharyngeal Reflux-Health-related Quality of Life score, and throat pain visual analog scale score.

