### Outcomes

#### Primary outcome

The RSI is a widely used scale for diagnosing and evaluating LPRD. It is a well-established patient self-report questionnaire and is a tool with publicly available data. The RSI scale contains 9 items, which are scored on a 6-point Likert scale (0–5), with a score of 0–45. The higher the score, the more severe the symptoms. RSI > 13 points will be considered possible patients with LPR [29]. RSI remains the “standard” in this field, although it has some shortcomings and limitations [30]. Therefore, we will select it as the primary outcome to assess the severity of reflux. Participants will be evaluated for changes in scale scores before the start of the experiment (after the informed consent will be obtained) and at 4, 12, and 24 weeks of the experiment (Fig. 2). The last of the nine items of the RSI is a complex GORD problem that includes heartburn, chest pain, indigestion, and acid reflux. Patients with dyspepsia may reach 5 points on the ninth item, which may be mistaken for patients with LPR. Referring to the report of a clinical trial, we will require that after the ninth item is removed, the score must be greater than or equal to 10 to be included [31]. Significant improvement will be defined statistically here, when the total score values will decrease by more than 50%. In addition, the valid rate will be defined as the proportion of patients showing significant and effective improvements.

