### Dx-pH monitoring

The oropharyngeal pH test is an important test for the objective diagnosis of LPR. Some researchers compared the ability of oropharyngeal and esophageal pH monitoring to predict the response of patients with suspected LPR to PPI treatment, indicating that the oropharyngeal probe has a higher positive predictive power than esophageal measurement [36]. All patients will be required to undergo Dx-pH testing before enrollment to determine whether they have acid, alkaline, or mixed reflux. Only patients with acid reflux will be included. Because PPI has a great effect on acidic and mixed reflux, it can alkalize the gas and liquid of reflux and reduce the activity of pepsin, but it has little effect on alkaline reflux [37]. In previous studies, because of the time and economic cost of pH testing, most patients are unwilling to perform pH monitoring again after treatment. Therefore, we will consider pH detection as a secondary outcome.

All outcomes will be measured at the four time points of the study. Dx-pH monitoring will be performed at baseline and 12 weeks. LPR-HRQL score, throat pain VAS score, and RFS will be assessed at baseline, 4, and 12 weeks. RSI will be evaluated at baseline, and 4, 12, and 24 weeks. The time schedule for the inclusion of participants, intervention, and evaluation is shown in Fig. 3.

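### The primary outcome is change in RSI, the 80% power is for the post-treatment score, and only unadjusted tests are named; adjusting for baseline RSI would remove the ambiguity and gain precision.

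*Protocol article*

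**What the plan says.** The abstract defines the primary outcome on the change scale: "The main outcome will be changes in the Reflux Symptom Index scores at 4, 12, and 24 weeks after treatment". The Primary outcome section does the same: "Participants will be evaluated for changes in scale scores before the start of the experiment" and at the later visits. Baseline RSI is therefore available for every patient; the Dx-pH monitoring section confirms that "RSI will be evaluated at baseline, and 4, 12, and 24 weeks".

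The Sample size section works on another scale. Its source figures are a level reached after three months of PPI treatment: "the RSI score was approximately 11.7 points, and the standard deviation was approximately 6". The planned difference of 4.5 points is also a difference in score after treatment. From this come 29 patients per group, 33 after allowing for 10% dropout, and a planned 35.

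The Statistical analyses section states the comparison in one general sentence: "Continuous variables will be compared using the t-test" or the Mann-Whitney U test. It mentions no baseline covariate and does not say which RSI quantity enters the test.

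**The concern.** A final score and a change from baseline have different variances, so a sample size worked out for one does not carry over to the other. Whether the change is the noisier of the two depends on how strongly baseline RSI predicts follow-up RSI. If the correlation is weak, subtracting baseline adds noise, and a trial sized on the final score is too small for the change.

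The protocol thus leaves open which quantity is tested, and for one of the two readings the stated power is not established. Both readings also ignore a baseline measurement that has already been taken. The Randomization section states balanced baseline RSI as an aim but describes no stratification on it, so the analysis is the natural place to use it.

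**Working it through.** **Inputs from the Sample size section:** difference 4.5; SD of post-treatment RSI 6; two-sided t-test; 80% power; 10% dropout; 35 recruited per group. Alpha is taken as 0.05, as in the Statistical analyses section. The Sample size section prints it with a percent sign, but 0.0005 would need 70 per group, so the stated 29 reproduces only with 0.05.

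**Assumed, because not given:** the correlation rho between baseline and follow-up RSI, shown from 0.2 to 0.7; the baseline SD, taken as 6 and then varied from 4 to 7.

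**1. The plan's own figure.** Standardised difference 4.5 / 6 = 0.75. The noncentral t calculation gives 28.9, so 29 per group, with power 80.1%. Dropout: 29 / 0.9 = 32.2, so 33. Both figures are reproduced, for the final score.

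**2. Patients likely to be evaluable.** 35 × 0.9 = 31.5; 31 per group is used below. Final-score power at 31 is 83%, whatever rho is.

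**3. SD under each analysis, with equal SDs.**
- Change score: 6 × sqrt(2(1 − rho))
- ANCOVA residual: 6 × sqrt(1 − rho²)

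For rho 0.3 these are 6 × sqrt(1.4) = 7.10 and 6 × sqrt(0.91) = 5.72.

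**4. Power at 31 per group, difference 4.5, two-sided 0.05.**

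| rho | SD of change | Power, change | ANCOVA SD | Power, ANCOVA | Power, final score |
|---|---|---|---|---|---|
| 0.2 | 7.59 | 63% | 5.88 | 84% | 83% |
| 0.3 | 7.10 | 69% | 5.72 | 86% | 83% |
| 0.5 | 6.00 | 83% | 5.20 | 92% | 83% |
| 0.7 | 4.65 | 96% | 4.28 | 98% | 83% |

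Charging ANCOVA one degree of freedom for the covariate changes none of these rounded figures.

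**5. Break-even for the change score.** Power reaches 80% at rho of about 0.50 with 29 per group and about 0.46 with 31.

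**6. Other baseline SDs.** With baseline SD s, the SD of change is sqrt(36 + s² − 12 × rho × s). At rho 0.3 and 29 per group, change-score power is 78%, 73%, 66% and 59% for s = 4, 5, 6 and 7. ANCOVA power does not depend on s; at this rho and n it is 84%.

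**7. Why ANCOVA settles the scale.** Subtracting baseline from both sides of a model that already contains baseline alters only the baseline coefficient. The treatment effect is the same whether follow-up RSI or change is the outcome, so the choice between the two no longer matters.

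**The case against.** The best counter-argument is that the Sample size section is the only place that ties a specific RSI quantity to a test, and that quantity is the score after treatment. On that reading the power is as stated, slightly better with the patients actually planned, and nothing falls short. This stands: the protocol is ambiguous, and it would be wrong to say that it commits to an unadjusted test of change. It is equally true that two sections define the primary outcome as change, so the other reading cannot be set aside.

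The size of any shortfall rests on a correlation and a baseline SD that the document does not give. From a correlation of about 0.5 upwards, with equal SDs, there is no shortfall. The RSI entry threshold could narrow the baseline SD, which helps the change score, or lower the correlation, which harms it. Against the final-score test the gain from adjustment is small when the correlation is low: 84% against 83% at 0.2.

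Three stronger readings might be inferred, and the document supports none of them.
- That the unadjusted comparison is biased by chance baseline imbalance. Under randomisation it is unbiased, and chance imbalance is already counted in its standard error.
- That adjustment guarantees 80% power. It still depends on SD 6 and a true difference of 4.5.
- That the choice between t-test and Mann-Whitney will be made on observed normality. The text links normality only to how data are summarised; a data-driven choice of test is a plausible inference but is not stated.

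Finally, covariate adjustment is often left to an analysis plan that is not shown here. That would excuse silence, but this protocol names its tests.

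**Conclusion.** The point holds as an efficiency improvement, together with a conditional power shortfall. The outcome is defined as change, the power was calculated for the final score, and the stated tests ignore baseline RSI. If change is tested without adjustment, power at about 31 per group is 63% to 69% for correlations of 0.2 to 0.3 and passes 80% only from a correlation of roughly 0.45 to 0.5, assuming a baseline SD of 6. If the final score is tested, power is about 83%.

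Apart from one degree of freedom, ANCOVA is never less efficient than either unadjusted test, and over the assumed range it gives 84% to 98%. The recommendation therefore does not depend on knowing the correlation; only the size of the gain does. The planned t-test is not invalid.

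**What to change.** In the Statistical analyses section, specify the primary RSI analysis as a linear model of follow-up RSI on treatment group with baseline RSI as covariate, reporting the adjusted mean difference with its 95% confidence interval. Apply it at week 12, the time point closest to the three months used for the sample size, or fit a mixed model over weeks 4, 12 and 24 with baseline RSI as covariate and name the contrast of interest. Use the same form for RFS, LPR-HRQL and throat pain VAS, which are also measured at baseline. Keep the Mann-Whitney test as a sensitivity analysis. State in the Sample size section that the calculation refers to the post-treatment score.

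Recruitment began on June 1, 2021, and participants and outcome assessors know the allocation. The change should therefore be a dated protocol amendment with the registry update that the quality assurance section already provides for, completed before any analysis. It needs no extra patients, visits or data.
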